**Fig. 1 Fig1:**
[figure not shown]
Schedule of trial procedures. *ALT* Alanine aminotransferase, *ECG* Echocardiography, *HIV* Human immunodeficiency virus, *TB* Tuberculosis

Participants will be instructed to attend unscheduled visits if they develop acute symptoms. For specific acute symptoms, investigations and management will be as follows: for diarrhoeal episodes (Division of AIDS [DAIDS] severity grade ≥ 3), a rectal swab and *Clostridium difficile* rapid test will be taken (C. Diff Quick Check Complete™; Alere) and if positive will be treated with metronidazole for 7 days. For acute respiratory exacerbations, sputum and nasal swabs will be taken and will be treated with amoxicillin-clavulanate for 10 days; if there is no improvement, a chest radiograph and culture for TB will be obtained. For febrile episodes, blood cultures, malaria slides and or malaria rapid diagnostic tests and rectal swabs will be taken, and management will be carried out according to national guidelines. For other acute symptoms, investigations and management will be carried out at the discretion of the treating clinician. A nasal swab, rectal swab, and sputum and blood samples will be collected at study visits for measurement of immune activation markers, investigation of antimicrobial resistance and assessment of changes in the gut and respiratory microbiome.

### Risks

Potential risks include an allergic reaction or adverse reaction to the medication or placebo. Examples of potential side effects include nausea, vomiting, diarrhoea and skin reactions. Each of these risks and any other unexpected outcomes will be monitored at study visits. Criteria for stopping the study drug are allergic reaction, QTc prolongation > 500 milliseconds, hepatic toxicity with ALT > 80 IU/L, concomitant use of drugs known to produce QTc prolongation, pregnancy during the course of the study and any adverse reaction with DAIDS severity grade > 3. In case of any serious adverse events, the institutional review boards and the data and monitoring safety board (DSMB) will be notified. Unblinding of treating physicians will be carried out in case of pregnancy or other events after decision by the DSMB.

### Outcome measures

The primary outcome is the mean difference between trial arms in FEV_1_ z-scores (generated using Global Lung Function Initiative reference standards) between trial arms at 12 months after initiation of the study drug, adjusted for site and baseline FEV_1_ z-score. The secondary outcomes are described in Table 2.

**Table 1 Tab1:** Inclusion/exclusion criteria

Inclusion criteria • Perinatally acquired HIV (self-report of no sexual debut or blood transfusions, a history of orphanhood owing to maternal HIV disease and/or a history of sibling death due to HIV, and characteristic clinical features (i.e., stunting, history of recurrent minor infections in childhood and planar warts) • Aged 6–19 years • On first- or second-line ART for ≥ 6 months • Chronic lung disease (FEV_1_ z-score less than −1 and < 12% improvement with bronchodilator) • Firm home address accessible in Blantyre/Harare and intending to remain there for 18 months • Stable caregiver for participants aged < 18 years • HIV status disclosed to the child (for those aged > 12 years) • Informed consent to participate in the trial (for those aged < 18 years, consent from guardian and assent from participant; for those aged ≥ 18 years, consent from participant)
Exclusion criteria • Any condition that may prove fatal during the study period • Diagnosis of tuberculosis at enrolment • Acute respiratory tract infection during enrolment • Pregnancy and breastfeeding • History of prolonged QTc syndrome or current or planned therapy with drugs likely to cause cardiac dysrhythmias • History of cholestatic jaundice or hepatic dysfunction associated with previous use of azithromycin or known hypersensitivity to a macrolide or ketolide drug • Prolonged QTc interval (> 440 milliseconds in males; > 460 milliseconds in females) • Creatinine clearance < 30 ml/minute • ALT > 80 IU/L • Concomitant use of digoxin and/or fluconazole • Lack of understanding of the study procedure or uncooperative behaviour

*Abbreviations: ALT* Alanine aminotransferase, *ART* Antiretroviral therapy, *FEV*
_*1*_ Forced expiratory volume in 1 second, *HIV* Human immunodeficiency virus

**Table 2 Tab2:** Secondary outcomes

Outcome	Time point
Time to first respiratory exacerbation	
Time to death	
Number of acute exacerbations	By 12 months
Number of hospitalisations	By 12 months
Number of mild, moderate and severe adverse events	By 12 months
Mean weight-for-age z-score adjusted for baseline	By 12 months
Incidence of infectious episodes (*Salmonella* typhi, malaria, gastroenteritis)	By 12 months
Durability of effect (FEV_1_ z-score)	18 months

*FEV*
_*1*_ Forced expiratory volume in 1 second

Other outcomes will be the effect of azithromycin on (1) diversity and composition of respiratory and gut microbiome of children with HIV-associated chronic lung disease, (2) antibiotic resistance of bacteria colonising the respiratory tract, and (3) biomarkers of systemic inflammation.

### Laboratory procedures

Nasopharyngeal and sputum samples will be frozen and stored at −80 °C for later batch processing, which will include routine bacterial culture for respiratory pathogens, antimicrobial susceptibility testing and 16S ribosomal RNA (rRNA) amplicon sequencing (microbiome analysis). Microbiome analysis of stool samples will also be done.

Archived plasma samples (isolated and stored at −80 °C) will be used to quantify the levels of soluble markers of immune activation and microbial translocation, including high-sensitivity C-reactive protein, d-dimers, interleukin-6, β_2_-microglobulin and soluble CD14 using multiplex bead assays (Luminex, Austin, TX, USA). Levels of bacterial 16S rRNA will be quantified using qRT-PCR to measure the extent of microbial translocation over time. The levels of these markers will be correlated with FEV_1_ z-scores and compared between trial arms.

### Data collection and management and analysis plan

Research nurses and assistants collect the data at baseline and follow-up and record it on electronic clinical record forms using Google Nexus™ tablets (Google, Mountain View, CA, USA) running OpenDataKit software. In both countries, data will be uploaded, processed and saved to a Microsoft Access database (Microsoft, Redmond, WA, USA) before being exported to Stata version 14.0 software and merged into a single database backed up on a regular basis. Consistency checks and checks for missing data are performed both at data entry and fortnightly once the database has been merged. Laboratory data will be recorded on paper forms and entered into the database using optical character recognition. Spirometric data will be uploaded directly from the spirometer. Echocardiographic data will be recorded on electronic clinical record forms, and these will be processed and saved to the Microsoft Access database for merging with the main trial database.

The primary analysis will be done on a modified intention-to-treat basis [29]. Secondary analyses will include a per-protocol analysis which will be defined using all adherence data prior to unblinding the study. Continuous outcomes will be compared between treatment groups, adjusting for site and baseline measures of the outcome and using linear regression to estimate the mean difference and corresponding 95% CI. Time-to-event outcomes will be assessed using Cox proportional hazards regression and graphically displayed using Kaplan-Meier estimates. Between-group comparisons of binary outcomes will be analysed with logistic regression to estimate ORs and 95% CIs. Count data (e.g., number of hospitalisations) will be analysed using Poisson regression to estimate incidence rate ratios and 95% CIs. All analyses will be adjusted for site. Pre-specified effect modification analyses will include site and baseline severity of lung disease.

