## Abstract

**Background:**

Human immunodeficiency virus (HIV)-related chronic lung disease (CLD) among children is associated with substantial morbidity, despite antiretroviral therapy. This may be a consequence of repeated respiratory tract infections and/or dysregulated immune activation that accompanies HIV infection. Macrolides have anti-inflammatory and antimicrobial properties, and we hypothesised that azithromycin would reduce decline in lung function and morbidity through preventing respiratory tract infections and controlling systemic inflammation.

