### Sample size and power

The following assumptions were made to calculate the sample size:Mean FEV_1_ z-score of −2.04 in the control groupPatients randomised in equal proportions to the two regimensUp to 25% of participants unassessable owing to loss to follow-up, death or suboptimal spirometric tracesNo change in FEV_1_ z-score in the control armDifference in the trial arm mean FEV_1_ z-scores ranging from 0.15 to 0.3, an effect assumed to be of clinical relevanceSD ranging from 0.55 to 0.82 to assess the impact of variability on the difference in mean value the study has power to detect

Under these assumptions, a sample size of 400 recruited participants and 300 participants with outcome data (25% unassessable based on previous studies of Zimbabwean children) will enable 80% power to detect a difference in trial arm means ranging between 0.17 and 0.23, an effect size (difference in means/SD) of 0.32 (Fig. 2).

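### Poisson regression is named for every count outcome with no allowance for over-dispersion, so 95% CIs for the more frequent recurrent events are likely to be too narrow

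*Protocol article*

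**What the plan says.** The analysis paragraph of the protocol article (Data collection and management and analysis plan) assigns one regression family to each type of outcome. For counts it says: "Count data (e.g., number of hospitalisations) will be analysed using Poisson regression to estimate incidence rate ratios and 95% CIs". It adds: "All analyses will be adjusted for site". No other covariate is named for the count model. It mentions no dispersion parameter, robust variance, random effect or alternative count model.

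Table 2 (Outcome measures) lists the outcomes that fall under this model, all assessed over the first 12 months:

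- "Number of acute exacerbations"
- "Number of hospitalisations"
- "Number of mild, moderate and severe adverse events"
- "Incidence of infectious episodes", covering *Salmonella* typhi, malaria and gastroenteritis

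The other four rows are two time-to-event outcomes, weight-for-age z-score and FEV1 z-score at 18 months. They use other methods.

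**The concern.** Poisson standard errors are correct only if, given arm and site, the variance of the count per child equals its mean. That fails when children differ in their underlying event rate for reasons the model does not contain. The events then concentrate in some children, and the variance exceeds the mean.

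The article gives reasons to think this plausible. Its rationale for the lung disease refers to recurrence: "This may be a consequence of repeated respiratory tract infections and/or dysregulated immune activation that accompanies HIV infection". Eligibility is broad (ages 6 to 19, any FEV1 z-score below −1, first- or second-line ART). Baseline severity is considered important enough for a prespecified effect-modification analysis, yet the stated count model adjusts only for site.

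The stake is the inference on a main clinical hypothesis, fewer exacerbations, and on the count of adverse events. If the intervals are too narrow, a chance difference between arms can be reported as a benefit or a harm.

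**Working it through.** **The plan's own figures.** The article states no event rate, dispersion or power for any count outcome, so there is no figure on this point to reproduce. Its numerical basis, "a sample size of 400 recruited participants and 300 participants with outcome data", concerns the primary outcome and is internally consistent on that score: 300/(1 − 0.25) = 400, and an effect size of 0.32 with 150 per arm gives power Φ(0.32 × √(150/2) − 1.96) = Φ(0.81) = 79%, against the stated 80%.

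**Inputs.** From the article: Poisson model, adjustment for site, 1:1 allocation, 400 recruited (200 per arm). Assumed, because the article gives neither: μ, the mean number of events per child, and k, the between-child dispersion. Two-sided 5% is inferred from the 95% CIs.

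**Formula.** Let child-specific rates follow a gamma distribution, so that the count has mean μ and variance μ + kμ². The variance-to-mean ratio is

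φ = 1 + kμ.

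For the log rate ratio with n children per arm and no true effect:

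- model-based Poisson SE = √(2/(nμ))
- true SE = √(2φ/(nμ))

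The ratio is √φ. Since n cancels, a larger trial does not cure the problem. The actual type I error is 2 × [1 − Φ(1.96/√φ)], and coverage is one minus that.

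| φ (assumed) | √φ | 1.96/√φ | Type I error | Coverage of nominal 95% CI |
|---|---|---|---|---|
| 1.0 | 1.00 | 1.96 | 5.0% | 95.0% |
| 1.1 | 1.05 | 1.87 | 6.2% | 93.8% |
| 1.5 | 1.22 | 1.60 | 11.0% | 89.0% |
| 2 | 1.41 | 1.39 | 16.6% | 83.4% |
| 3 | 1.73 | 1.13 | 25.8% | 74.2% |

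**One case in full.** With n = 200, μ = 0.5 and k = 1, φ = 1.5. The model-based SE is √(2/100) = 0.141 and the true SE is √(3/100) = 0.173. Around a rate ratio of 1, the reported interval would be exp(±1.96 × 0.141), or 0.76 to 1.32. The correct one is exp(±1.96 × 0.173), or 0.71 to 1.40.

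**Simulation check.** Gamma-Poisson counts, 200 per arm, no arm effect, equal follow-up, site in the model, 2000 replicates per scenario. Rejection rates at nominal 5%:

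| μ | k | φ | Model-based SE | Robust SE |
|---|---|---|---|---|
| 0.1 | 1 | 1.1 | 6.7% | 5.7% |
| 0.1 | 4 | 1.4 | 8.6% | 4.9% |
| 0.5 | 0 | 1.0 | 5.3% | 5.4% |
| 0.5 | 1 | 1.5 | 10.1% | 4.6% |
| 0.5 | 2 | 2.0 | 16.9% | 6.1% |
| 1 | 1 | 2.0 | 17.0% | 5.5% |
| 2 | 1 | 3.0 | 26.7% | 5.2% |

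The simulation error is about 0.5 percentage points at a true rate of 5%. The results agree with the formula. They also show that, for a given k, the inflation grows with event frequency, and that robust standard errors keep the error at 4.6% to 6.1% throughout.

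**The case against.** The strongest reply is that this rests on silence. The article names a model family and an estimand, not a variance estimator. The variance estimator is often left to an analysis plan, which is not shown here. Poisson with robust standard errors would contradict nothing in the sentence. That stands in part: a reader might infer that the trial is committed to uncorrected model-based errors, and the text does not go that far. But the article does positively name the model and its adjustment without qualification. Read at face value, that gives model-based intervals, and a better method can be stated in a few words. If the analysis plan already has it, the point is closed by confirming so.

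Three further inferences are tempting and go beyond the document.

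- *That the counts will certainly be over-dispersed.* No rates or dispersion are reported. The rationale about repeated infections is a hypothesis on how the lung disease arose, not evidence of clustering over 12 months of follow-up. Clustering is plausible, not shown.
- *That every count is badly affected.* At an assumed mean of 0.1 events per child, the error is only about 7% to 9%. Any of the less frequent events could fall in that region.
- *That most secondary efficacy outcomes are involved.* In Table 2 it is four rows of eight. Setting adverse events aside leaves three of seven. A majority appears only if the infections are counted separately, as the abstract lists them. Exacerbations are also analysed as time to first event by Cox regression, which does not use the Poisson variance for repeat events.

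**Conclusion.** The point holds in a conditional form. As stated, the method for counts gives valid intervals only if the variance equals the mean given arm and site. Departure from that is likely for the more frequent recurrent outcomes, probably exacerbations and adverse events. Over the assumed range of variance-to-mean ratio from 1.1 to 3, the true type I error runs from about 6% to about 26%. Where in that range each outcome falls cannot be derived from the article.

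The consequence is limited to the confidence intervals and p-values of these secondary outcomes. The rate ratios themselves remain consistent, and neither the primary FEV1 comparison nor the sample size depends on this model. It should be corrected because the remedy is cheap and has to be fixed before the data are seen, but it does not threaten the trial's main result.

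**What to change.** Before unblinding, fix one method for all count outcomes: Poisson regression with robust (sandwich) standard errors, log person-time as offset, and arm and site as covariates. If the data hold several records per child, the robust variance should be clustered on the child. Negative binomial regression with the same terms can be a sensitivity analysis for the frequent outcomes. It should not be a main method with a fallback on non-convergence, because the model would then be chosen by the data.

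The cost is one line of text and one option in the regression command, with no new data. Intervals will usually be somewhat wider where counts are over-dispersed, which is the purpose. Robust standard errors are slightly more variable when events are few, so for the rarest outcomes the gain is small.

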### Sample size and power

The following assumptions were made to calculate the sample size:Mean FEV_1_ z-score of −2.04 in the control groupPatients randomised in equal proportions to the two regimensUp to 25% of participants unassessable owing to loss to follow-up, death or suboptimal spirometric tracesNo change in FEV_1_ z-score in the control armDifference in the trial arm mean FEV_1_ z-scores ranging from 0.15 to 0.3, an effect assumed to be of clinical relevanceSD ranging from 0.55 to 0.82 to assess the impact of variability on the difference in mean value the study has power to detect

Under these assumptions, a sample size of 400 recruited participants and 300 participants with outcome data (25% unassessable based on previous studies of Zimbabwean children) will enable 80% power to detect a difference in trial arm means ranging between 0.17 and 0.23, an effect size (difference in means/SD) of 0.32 (Fig. 2).

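### The detectable differences of 0.17 to 0.23 do not follow from 300 analysed participants, SDs of 0.55 to 0.82 and an effect size of 0.32

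*Protocol article*

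**What the plan says.** The section 'Sample size and power' of the protocol article assumes equal allocation, up to 25% of participants unassessable, and an SD of the FEV1 z-score between 0.55 and 0.82. It gives the SD range in order to show how variability changes the difference that the trial can detect. From these assumptions it derives "a sample size of 400 recruited participants and 300 participants with outcome data", and states that this gives "80% power to detect a difference in trial arm means ranging between 0.17 and 0.23, an effect size (difference in means/SD) of 0.32". The sentence thus equates the range of differences with a single effect size.

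The section gives no significance level and no correlation between baseline and 12-month values. Under 'Outcome measures', the primary comparison is to be "adjusted for site and baseline FEV_1_ z-score". The analysis plan section reports continuous outcomes "using linear regression to estimate the mean difference and corresponding 95% CI".

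**The concern.** The sentence ties three things together: a range of SDs, a single effect size defined as difference divided by SD, and a range of differences. Any two of them fix the third, and the three given here do not agree. The disagreement needs no assumption about the significance level, because 0.32 × 0.82 = 0.26, not 0.23.

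This is the article's only statement of power for the primary outcome. It tells readers what size of effect the trial was built to find. If the upper figure is too small, the design looks more sensitive at high variability than its stated inputs make it.

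**Working it through.** **Inputs from the protocol article.** 400 recruited, 25% unassessable, 1:1 allocation, 80% power, SD 0.55 to 0.82, effect size 0.32, differences 0.17 to 0.23.

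**Assumption.** Two-sided 5%. It is not stated, but it matches the planned 95% confidence intervals and reproduces the stated 0.32.

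**Step 1: reproduce what can be reproduced.**
- Analysed: 400 × 0.75 = 300, or 150 per arm. This agrees.
- Detectable standardised difference: (1.960 + 0.842) × √(2/150) = 0.3235 (0.3245 with the t distribution). The stated 0.32 agrees, and it is the value for an unadjusted comparison.

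**Step 2: convert to z-score units.**

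| SD | 0.32 × SD | 0.3235 × SD | Stated difference | Stated difference / SD |
|---|---|---|---|---|
| 0.55 | 0.176 | 0.178 | 0.17 | 0.31 |
| 0.82 | 0.262 | 0.265 | 0.23 | 0.28 |

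Read backwards, an effect size of 0.32 with differences of 0.17 and 0.23 implies SDs of 0.17/0.32 = 0.53 and 0.23/0.32 = 0.72, not 0.55 and 0.82.

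**Step 3: power for the stated differences, 150 per arm, unadjusted.** Power = Φ(d/√(2/150) − 1.960), with d = difference/SD and √(2/150) = 0.1155.
- 0.23 at SD 0.82: d = 0.2805, so Φ(2.429 − 1.960) = 68.1% (t-based 67.8%).
- 0.17 at SD 0.55: d = 0.3091, so Φ(2.677 − 1.960) = 76.3% (t-based 76.1%).

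**Step 4: can one other set of settings give both ends?** For fixed numbers, significance level, power and baseline correlation, the detectable difference is proportional to the SD. The ratio of the differences must then equal the ratio of the SDs. The SD ratio is 0.82/0.55 = 1.49; the ratio of the differences is 0.23/0.17 = 1.35. Rounding does not close the gap: the differences allow at most 0.235/0.165 = 1.42, and the SDs require at least 0.815/0.555 = 1.47. Specific variants confirm this:

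| Variant | SD 0.55 | SD 0.82 |
|---|---|---|
| One-sided 5%, 150 per arm, 80% power | 0.158 | 0.235 |
| Two-sided 5%, 200 per arm (no loss), 80% power | 0.154 | 0.230 |
| Two-sided 5%, 150 per arm, 90% power | 0.206 | 0.307 |
| Two-sided 5%, 200 per arm, 90% power | 0.178 | 0.266 |

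**Step 5: baseline adjustment.** With correlation ρ, the SD is replaced by SD × √(1 − ρ²). The values of ρ are assumptions, as the article gives none.

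| ρ | Power for 0.23 at SD 0.82 | Detectable at SD 0.55 | Detectable at SD 0.82 |
|---|---|---|---|
| 0 | 68% | 0.178 | 0.265 |
| 0.3 | 72% | 0.170 | 0.253 |
| 0.5 | 80% | 0.154 | 0.230 |
| 0.6 | 86% | 0.142 | 0.212 |

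A detectable difference of exactly 0.17 at SD 0.55 needs ρ of about 0.3, and one of 0.23 at SD 0.82 needs ρ of about 0.5. No single correlation returns the stated range.

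**The case against.** The strongest reply is that the planned analysis adjusts for baseline, while the 68% belongs to an unadjusted comparison. This stands as a limit on the conclusion. At a correlation of 0.5 or more, both stated differences would have at least 80% power under the planned model. A reader might infer from the arithmetic that the trial lacks its claimed power at the upper SD; the article does not support that, because the correlation is unknown. The reply does not rescue the sentence, which names no correlation and quotes the unadjusted 0.32 beside the differences.

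A second reply is that the lower end is only 0.008 out. That is fair, and the point rests on the upper figure.

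Two further inferences are tempting and should not be drawn:
- *That the 25% loss was left out.* The figure of 0.23 at SD 0.82 does match 400 analysed, but the same calculation gives 0.154 at SD 0.55, not 0.17. A different upper SD, some baseline adjustment or a typing error are equally open, and Fig. 2, which holds the calculations, could not be read here.
- *That the trial fails its own target at 0.15.* The article lists 0.15 to 0.3 as assumed differences and nowhere claims 80% power at 0.15. Its own lower limit of 0.17 already shows that 0.15 is not reached.

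Finally, a null result will be read from its confidence interval rather than from the power statement, so the effect on interpretation is limited.

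**Conclusion.** The concern holds as an error in a stated figure. The 300 analysed and the effect size of 0.32 are sound; the range "a difference in trial arm means ranging between 0.17 and 0.23" is not what they give over the stated SDs. Under a two-sided 5% test without adjustment the range is about 0.18 to 0.27. The discrepancy is minor at the lower end. At the upper end it is about 0.035 z-score units (0.265 − 0.230), or some 12 percentage points of power.

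The 68% rests on the assumed significance level and on no gain from baseline adjustment. The internal contradiction rests on neither. The corrected upper value still lies within the 0.15 to 0.3 that the article treats as clinically relevant, so nothing here calls for a larger trial.

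**What to change.** Restate the sentence in 'Sample size and power' along these lines: *300 participants with outcome data give 80% power (two-sided 5%) to detect a difference of about 0.18 (SD 0.55) to 0.27 (SD 0.82), an effect size of 0.32, before any gain from baseline adjustment.* The significance level should be confirmed by the trial team.

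Alternatively, if 0.17 to 0.23 came from another SD range or from an assumed baseline correlation, state those inputs and give an effect size that agrees with them. The SD range should not be altered merely to make 0.23 come out.

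Correct Fig. 2 if it carries the same figures. The cost is one sentence and possibly a figure. Recruitment, outcomes and the analysis are unchanged; the stated sensitivity at the upper SD becomes less favourable.
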